# The effect of paramedic training on pre-hospital trauma care (EPPTC-study): a study protocol for a prospective semi-qualitative observational trial

**DOI:** 10.1186/1472-6920-14-32

**Published:** 2014-02-15

**Keywords:** Paramedic, Pre-hospital, Trauma, Training, PHTLS, Medical education

## Abstract

**Background:**

Accidents are the leading cause of death in adults prior to middle age. The care of severely injured patients is an interdisciplinary challenge. Limited evidence is available concerning pre-hospital trauma care training programs and the advantage of such programs for trauma patients. The effect on trauma care procedures or on the safety of emergency crews on the scene is limited; however, there is a high level of experience and expert opinion.

**Methods:**

I – Video-recorded case studies are the basis of an assessment tool and checklist being developed to verify the results of programs to train participants in the care of seriously injured patients, also known as “objective structured clinical examination” (OSCE). The timing, completeness and quality of the individual measures are assessed using appropriate scales. The evaluation of team communication and interaction will be analyzed with qualitative methods and quantified and verified by existing instruments (e.g. the Clinical Team Scale). The developed assessment tool is validated by several experts in the fields of trauma care, trauma research and medical education. II a) In a German emergency medical service, the subjective assessment of paramedics of their pre-hospital care of trauma patients is evaluated at three time points, namely before, immediately after and one year after training. b) The effect of a standardized course concept on the quality of documentation in actual field operations is determined based on three items relevant to patient safety before and after the course. c) The assessment tool will be used to assess the effect of a standardized course concept on procedures and team communication in pre-hospital trauma care using scenario-based case studies.

**Discussion:**

This study explores the effect of training on paramedics. After successful study completion, further multicenter studies are conceivable, which would evaluate emergency-physician staffed teams. The influence on the patients and prehospital measures should be assessed based on a retrospective analysis of the emergency room data.

**Trials registration:**

German Clinical Trials Register, ID DRKS00004713.

## Background

Accidents are the leading cause of death in adults prior to middle age [1]. A patient collective is concerned which could particularly benefit from rapid recovery after an accident. In addition to the personal suffering and loss of so-called human capital (in work and leisure activities), the economic costs are relevant and have an effect on the gross national product [2]. The economic costs of traffic accidents in Germany amount to 31 billion euros per year [3].

In recent years, there have been a number of indications of the importance of study findings concerning trauma care, including the following: 1) the introduction of regional trauma-networks [4,5]; 2) a White Paper from the German Trauma Society [6,7]; 3) increased training of emergency department teams [8] and training programs in emergency medical services [9]; 4) the establishment of the TraumaRegister DGU® of the German Trauma Society [10]; and 5) the German S3 – Guideline on Treatment of Patients with Severe and Multiple Injuries (2011) [1].

In the 1970s, “Advanced Trauma Life Support” (ATLS) introduced standardized treatment of trauma patients in emergency departments. Probable total of approximately 2 million physicians are trained in the program worldwide [11]. The global ATLS program is a condition for certification for trauma centers in Germany [12]. Münzberg et al. showed that since 2003, ATLS has performed with high ratings based on evaluation by the participants [11]. Based on the “lowest common denominator”, ATLS is a concept for training the physicians dealing with severe injured patients in the emergency departments in Germany [13]. Ruchholtz et al. showed in the 1990s that procedures based on the guidelines could improve the care of emergency room patients [14]. Evidence of the effect on patient outcome is lacking [15].

The interface between emergency medical services (EMS) and emergency departments in the treatment of seriously injured patients benefits from uniform standards of care based on identical medical-scientific knowledge and communication with a “common language” to avoid errors and to improve priority-based patient care [16].

The treatment of severely injured patients is particularly challenging because these injuries are rare [17] and require multi-disciplinary team work and complex and comprehensive therapy [18]. Pre-hospital care is in parts associated with considerable technical effort.

The pre-hospital care of severely injured patients was essentially characterized in the past by the two following systems: “stay and play” or “load and go” [19]. In recent decades, pre-hospital trauma care has been supplemented by the findings of military medical treatment [20] and appear to approach each other [21].

Pre-hospital treatment has to establish the initial treatment strategies and be priority-oriented. The available data are inadequate, although field experiences and expert opinions are extensive.

The existing trauma care training programs such as the Pre-Hospital Trauma Life Support (PHTLS) or ATLS programs lead to more subjective safety levels of the participants regarding the care of trauma patients [22,23]. The extent of the effect of this training on the quality of the process and especially on the quality of the primary outcomes of modern EMS systems is not clear [24]. The introduction of a training program such as PHTLS in less developed systems results in a measurable change [25]. Studies that evaluated the outcome of patients after rescue and treatment according to the PHTLS standards have shown no significant advantage over currently established principles of trauma care [26,27]. Standardized training programs such as PHTLS are increasingly integrated into the training or education of EMS staff [28,29]; however, the differences in the current standard of care from the recommendations of PHTLS are unknown. A concrete comparison of the PHTLS content with the current guidelines for the treatment of multiple traumas is pending.

The participants evaluate PHTLS courses very positively, although there are no published evaluations. A subjective assessment by the participants was collected after the PHTLS TEAM (PHTLS at medical school) training, which suggests an improvement in the scenario based on the care of severely injured patients [23]. Particularly in the area of “non-technical skills”, various assessment instruments have been developed that assess communication, team interaction, and decision making [30-34].

There is no suitable measuring instrument to ensure the effect of training objectively like the processes, strategic decisions, skills and medical aspects of treatment.

This study will evaluate the effect of PHTLS courses on the participants because its effect on patient outcome as known is not measurable.

### Hypotheses

Using a novel assessment tool (2.4.1), the following hypotheses will be tested:

▪ The introduction of PHTLS leads to improved quality of the documentation of actual field operations.

▪ The introduction of PHTLS leads to structured patient care by the ABCDE scheme [35], with priority-based interventions in case-based scenario training.

▪ The introduction of PHTLS leads the participants to a subjectively better and safer application of the principles.

### Trial design

This trial is designed as an interventional, single arm – uncontrolled, open study. It is a single-center, prospective, semi-qualitative observational trial.

## Methods

### Study setting

The study is performed in the EMS of the city of Wiesbaden and Rhein-Taunus-Kreis (Germany). The operational area in Wiesbaden has five commissioned EMS agencies (four charities, one private provider). The EMS in Wiesbaden has 375 paramedics and serves 462 098 inhabitants.

With regard to the training, close cooperation occurs with the neighboring Rheingau-Taunus-Kreis area. In the context of various difficulties and problems, the controlling authority enabled 301 paramedics from both EMS services to attend the PHTLS courses to create uniform structures and principles [28].

### Eligibility criteria

Included in the study are all the employed paramedics and emergency medical technicians (EMTs) of the participating institutions (ASB, DRK, MHD, private) of the emergency medical services of Wiesbaden and Rheingau-Taunus-Kreis. Excluded are all the participants not involved with the participating institutions.

### Interventions

Paramedical personnel are trained in the care of trauma patients, and the worldwide standardized and certified training program “PHTLS” (Pre Hospital Trauma Life Support) is used.

PHTLS provider courses focus on the professional groups involved in EMS (EMT, paramedics, emergency physicians) for the pre-hospital care of trauma patients and are currently well established in Germany. Among other participants, the helicopter crews of the DRF German Air Rescue will be trained in PHTLS, as well as the German armed forces, which have established PHTLS courses for mission preparation. Thus, PHTLS courses are merged seamlessly with ATLS courses for clinical care in emergency departments [8].

The central link between the PHTLS and ATLS courses is uniform communication and the priority-based approach [22].

In the two-day courses, the participants obtain a complete procedure for the structured treatment of trauma patients, in addition to trauma-specific skills; the classes conclude with a written and practical exam.

PHTLS courses are characterized by the extensive variety in the teaching methods (lectures, practical case studies), with a close instructor- participant ratio (1:3), many practice activities and continuous interaction.

In addition to various skills, the priority-based structure, ABCDE (Airway, Breathing, Circulation, Disability and Exposure), is taught and practiced in scenario-based training sessions. The “ABCDE” method provides structure for patient treatment and ensures that other therapeutic measures are objectified [15].

The PHTLS manual (2^nd^ German edition), which forms the basis for the German PHTLS courses [35], is sent to the participants before the course and is intended to provide the course content with the following priorities:

▪ Safety for EMS staff and patients

▪ Involvement of the accident kinematics in the assessment

▪ Priority-based treatment-principles, “treat first what kills first”

▪ Rapid and correct c-spine immobilization

▪ Immediate repair of airway (A) problems

▪ Evaluation of the ventilation, rapid oxygen administration and treatment of tension pneumothorax

▪ Stop external bleeding and minimization of internal bleeding, e.g. with the pelvic sling

▪ Positioning of axis fractures, and immobilization of the patient if necessary

▪ Treatment of hypothermia

▪ Insertion of iv-lines and fluid resuscitation

▪ Neurological assessment with GCS (Glasgow Coma Scale) and pupil status

▪ Team communications with clear instructions and early clarification to the receiving hospital

As part of the so-called secondary survey, the PHTLS courses provide a SAMPLE scheme with **s**ymptoms, **a**llergies, **m**edications, **p**atient history (including the medical history), the **l**ast oral intake and information about the **e**vent that led to the emergency situation.

The PHTLS courses require a baseline-scenario at the beginning of the course, in which the participants treat a patient in a standardized scenario-based case, without help or feedback from the instructors. The participants obtain an impression of their work before the course. During the second day, a clear shift towards a structured treatment is typically recognized.

### Outcomes

Three outcome measurement methods are used:

#### Assessment tool

The Assessment-Tool has to be used to evaluate objectively the processes and skills during the scenarios. This method is also applied as “objective structured clinical examination” (OSCE) in medical schools [36-39] and used in emergency medical education, too [40,41]. The assessment tool will be designed for the video-based outcome measurement with defined endpoints.

The assessment tool shall take into account three main aspects:

▪ The educational content of the PHTLS courses including oxygen administration, c-spine immobilization and treatment algorithms.

▪ Established assessment instruments such as the Clinical Team Scale (CTS) for the validation of teamwork, team communication and clinical decision making.

▪ Aspects, which are noticeable in the analysis of the scenarios.

Verifiable items are developed from the PHTLS curriculum and from the established measurement instruments, which can be assessed and quantified using an instrument such as the Likert Scale.

Various video-recorded scenarios are used to perform a qualitative content analysis in a non-reactive observation. The relevant features are clustered and transcribed to obtain quantifiable items.

The items are evaluated independently of the measurement scale and summarized as a total score. The fulfilled items will be chronologically registered to analyze the diagnosis procedure and interventions.

Validation of the assessment tools with regard to objectivity and reliability should be based on two scenarios by experts in the fields of emergency medicine, medical education and traumatology. The number of experts will result in a ratio of the items.

The inter-rater reliability, which is the degree of agreement among the experts in the application of the assessment tool, can be verified using Fleiss’ kappa correlation, for which a significance level is set.

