## Discussion

The aim to evaluate the effect of the training or the effect of the program on the patient outcome is understandable, complex and difficult. This study attempts to evaluate the effect of the training on the participants’ behavior.

This is a single-center study and based on scenarios of the treatment given to patients by paramedics. There is interest in developing a multi-center assessment tool. Concrete efforts will be made after the completion of this study to apply the tool for evaluation of emergency physician-based teams including air rescue personnel.

We are aware that the video analysis is influenced by a variety of factors. In addition, the result of the scenario-based patient care is not to transfer 1:1 to the real patient care. To increase the comparability and consistency, a member of the research group will supervise the recordings or even leads them through. Time t0 records are parallel, and the scenarios are directed by leading instructors briefed on the key points and identical criteria to apply to all the cases. An identical situation occurs with t1, with the difference being that in t1, the cases are sequential instead of parallel.

Initially it was planned to visualize the individual measures on a timeline. However, the flow in the scenario is disturbed by the information from the instructors, for example vital signs or by questions from the participants, so it does not seem sensible to use the real-time analysis. In addition, a range of skills such as laying intravascular access or prepare infusions are not real performed.

The results of the questionnaire for the subjective assessment of the participants should be available without special bias, especially we expect a very high response rate. The evaluation of the EMS-protocols focuses on three items, which are trained in the course. But since the SAMPLE scheme is widely used, it remains to be seen how the degree of compliance prior to the course and a possible change is measurable.

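### No masking of video raters to time point is stated for a partly judgement-based score in an open before-after study, and Fleiss' kappa cannot reveal a shift that all raters share

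*Protocol article*

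**What the plan says.** Under Trial design: "This trial is designed as an interventional, single arm – uncontrolled, open study". No exception is made for those who assess outcomes.

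Under Outcomes, Assessment tool, the aim is objectivity: "The Assessment-Tool has to be used to evaluate objectively the processes and skills during the scenarios". It continues: "The assessment tool will be designed for the video-based outcome measurement with defined endpoints". Items come from the course curriculum and from established instruments covering teamwork, communication and clinical decision making, "which can be assessed and quantified using an instrument such as the Likert Scale". They are summed to a total score, and fulfilled items are also logged in order of occurrence.

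Two safeguards on rating are described, both in that section. The first is a validation step: "Validation of the assessment tools with regard to objectivity and reliability should be based on two scenarios by experts". The second is inter-rater agreement, which "can be verified using Fleiss’ kappa correlation, for which a significance level is set". The article does not say who scores the study recordings, in what order, or whether they know the time point.

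The Bias section covers prior knowledge, the acting of the patient role, instructors, participant motivation, a Hawthorne-type effect, and technical and organisational faults. It does not mention rater expectation.

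The Discussion adds, as a measure for comparability and consistency, that "a member of the research group will supervise the recordings or even leads them through". It then says that briefed leading instructors direct the scenarios.

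**The concern.** The video comparison sets t0 against t1 with no control group, and the plan states in advance which way it should go. The Hypotheses section predicts more structured care after the course, and the Interventions section says that a shift towards structured treatment is typically seen by the second day. A rater who knows or guesses that a recording is post-course has a reason to be more generous on any item that needs judgement.

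If that happens, the extra points at t1 cannot be told apart from learning. Nothing in a single-arm design subtracts them, and the agreement statistic does not expose them. The video-based hypothesis could then be supported, wholly or in part, by how the recordings were scored.

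**Working it through.** **1. The plan's own counts (Number of participants, Video recording).** At t0, 14 courses × 4 recordings = 56 teams, and 56 × 3 = 168 participants. At t1, 14 × 12 = 168 teams, given as an upper limit. Both reproduce. No effect size, SD, significance level or power is stated for the video score. The 0.05 level belongs to the questionnaires and the 0.1 level to the EMS protocols.

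**2. Where a rater shift goes.** Let δ be the true change in mean score and b the mean extra score that raters give at t1 because they expect improvement. Then the expected value of (mean at t1 − mean at t0) is δ + b. A control group scored by the same raters at the same times could help to estimate b; here there is none.

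**3. What kappa can show.** Fleiss' kappa compares raters with each other on the same recordings. If every rater adds the same b to t1 recordings, they still agree with each other. High kappa is therefore compatible with b = 0 and with b > 0.

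**4. Illustration of size.** These assumptions are not in the article: score standardised to SD 1, independent recordings, two-sided level 0.05, normal approximation, δ = 0.

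SE = √(1/56 + 1/168) = √0.02381 = 0.154

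P(p < 0.05) = Φ(b/SE − 1.96) + Φ(−b/SE − 1.96)

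| Shared shift b (SD) | b/SE | P(p < 0.05) |
|---|---|---|
| 0 | 0 | 0.05 |
| 0.1 | 0.65 | 0.10 |
| 0.2 | 1.30 | 0.25 |
| 0.3 | 1.94 | 0.49 |
| 0.4 | 2.59 | 0.74 |
| 0.5 | 3.24 | 0.90 |

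Because 168 is a maximum, the lower case of 56 recordings at both times is also useful. There SE = √(2/56) = 0.189. A shift of 0.2 SD gives b/SE = 1.06 and probability 0.18; a shift of 0.5 SD gives b/SE = 2.65 and probability 0.75.

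**5. Can a rater tell the time point from the recording?** Two features in the article suggest so. In the Bias section, a fellow participant plays the patient in the baseline scenario and an instructed mime does so in the case studies. In the Discussion, t0 cases run in parallel and t1 cases in sequence. Removing labels would therefore mask raters only in part.

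**The case against.** The strongest objection is that this rests on silence. The article is a condensed account, the full protocol is not shown, and file coding or rater allocation may be settled there. The word open in a one-line design label need not describe the video assessors; participants cannot be blinded to a two-day course in any case. This stands in part. A reader might infer that scoring is unmasked. The article does not say so: it neither names the scorers nor says that they know the time point, and the text is compatible with either arrangement.

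A reader might also infer that research staff lead the very scenarios they later score. The documents do not support that. In the Discussion sentence, what the research-group member supervises or leads is the recordings, and the next sentence gives the direction of the scenarios to instructors. Even if staff did lead scenarios, that would affect how the case is run. It becomes rater bias only if the same people score, which is nowhere stated.

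Further, the tool is still in development, the items are meant to be verifiable, and the Likert scale is named only as an example, so the share of judgement in the total is unknown. The size of any shift is also unknown, and teams are nested in 14 courses, so independence is an approximation. All of this stands and limits the figures to an illustration.

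What remains is not mere silence. The article claims objectivity and describes how rating quality will be checked, and the agreement check cannot detect the error most likely in this design. Its bias list is detailed and leaves that error out, while the text itself describes features that can give the time point away.

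**Conclusion.** The point holds as a missing safeguard. The outcome includes judgement-based ratings, the study is declared open and uncontrolled, the expected direction is known, no masking of video raters is stated, and agreement between raters does not protect against an expectation they share. Any such shift enters the estimated training effect in full.

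The conclusion does not depend on a particular size. The figures of about 25% at 0.2 SD and about 90% at 0.5 SD show only that a moderate shared shift would be enough to matter. They rest on an assumed shift, an assumed 5% level, independence, no true effect, and the maximum number of t1 recordings; with 56 at each time they fall to about 18% and 75%. They do not describe this study's actual error rate. This is a cheap improvement, and since the article reports recordings and tool development as still in process, the scoring rules could still be set.

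**What to change.** Add a short scoring rule to the Assessment tool section:

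- Give each recording a random file number and remove date, course and time-point labels.
- Score t0 and t1 files, and t2 files where available, in one random order.
- Draw scorers from the experts already planned for the validation, and let no one score a recording that they taught, led or supervised.
- Report the observable done/not-done items separately from the Likert items. The former leave less room for expectation and serve as a check on the latter.
- Add rater expectation to the Bias section, and state there that masking is partial because the patient role and the parallel or sequential set-up can reveal the time point.

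The cost is file renaming and a random scoring list. The downside is that scoring has to wait until both t0 and t1 files are available. No extra recordings or participants are needed.

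### A significance test of Fleiss' kappa does not show that raters agree well enough, and item-level kappa does not establish the reliability of the total score that is analysed

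*Protocol article*

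**What the plan says.** The Assessment tool section (Methods, Outcomes) describes items that "can be assessed and quantified using an instrument such as the Likert Scale". It continues: "The items are evaluated independently of the measurement scale and summarized as a total score". For the quality check, "Validation of the assessment tools with regard to objectivity and reliability should be based on two scenarios", rated by experts from three fields. Agreement among these experts "can be verified using Fleiss’ kappa correlation, for which a significance level is set".

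No value is given for that significance level, and no minimum kappa, confidence interval or reliability measure for the total score is named. The number of raters is not a figure either: "The number of experts will result in a ratio of the items".

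Statistical methods then makes the sum score the quantity that is summarised by mean or median and compared between measuring points. The single items are not compared there.

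**The concern.** The video endpoint depends on a new instrument. The Background says that no suitable instrument exists, and the Hypotheses section rests on this tool. The inter-rater check is therefore a main safeguard for the endpoint, and as described it has three weaknesses.

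1. **Criterion.** A significance level attached to kappa tests the hypothesis that kappa is zero. Rejecting it shows agreement better than chance, not adequate agreement.
2. **Scale.** Fleiss' kappa treats categories as nominal. On a five-point item, a 4 against a 5 counts as the same disagreement as a 1 against a 5.
3. **Target.** Agreement on items is related to the reliability of their sum, but it does not determine it. Pooled over items, kappa also rewards raters for agreeing on which items are usually performed, and this does not help to tell teams apart.

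At stake is the precision of the comparison between t0 and t1. If teams are scored by single raters with purely random error, the variance of the score is the true variance divided by the reliability, so a reliability of 0.5 doubles it. A mean difference is biased only if rater error differs between time points.

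**Working it through.** The article has no kappa, rater number, item number or precision figure to reproduce. Assumed inputs are 10 to 50 items, 3 to 15 raters and a two-sided level of 0.05. From the article come two scenarios, a Likert scale as an example, and a total score as the endpoint.

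**Smallest significant kappa.** With N rated units (items × scenarios), n raters, category proportions p and q = 1 − p, the null standard error is

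SE0 = sqrt(2 / (N·n·(n − 1))) × sqrt((Σpq)² − Σpq(q − p)) / Σpq.

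For two categories Σpq(q − p) = 0, so the second factor is 1 at any prevalence. For five equally used categories Σpq = 0.8 and Σpq(q − p) = 5 × 0.16 × 0.6 = 0.48, so the factor is sqrt(0.64 − 0.48) / 0.8 = 0.5. The smallest significant kappa is 1.96 × SE0.

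| Items × 2 scenarios | Raters | Scale | SE0 | Smallest significant kappa |
|---|---|---|---|---|
| 20 | 3 | yes/no | 0.1291 | 0.253 |
| 40 | 3 | yes/no | 0.0913 | 0.179 |
| 40 | 5 | yes/no | 0.0500 | 0.098 |
| 40 | 5 | 5 categories | 0.0250 | 0.049 |
| 100 | 5 | yes/no | 0.0316 | 0.062 |
| 100 | 15 | 5 categories | 0.0049 | 0.010 |

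The first and last rows are the extremes of the assumed range. At a level of 0.10 the range is 0.008 to 0.212. The formula treats items within a scenario as independent. That is doubtful, but the standard test makes the same assumption.

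**Ordinal items.** I simulated 100 units rated by 5 raters, with a normal latent score cut into five equally used categories. A latent ICC of 0.75 gave an unweighted kappa of 0.29 against an ICC of the ratings of 0.69. A latent ICC of 0.80 gave 0.33 against 0.75. Reasonable ordinal agreement can therefore look poor.

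**Items against total score.** For a sum over 25 items, the latent ICC is approximately team variance / (team variance + rater variance + error variance / 25).

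- Team SD 0.5, no rater differences, error SD 0.8: 0.25 / (0.25 + 0.64/25) = 0.91. Simulated with five-point items and 5 raters, the sum-score ICC is 0.89 and the item kappa 0.07.
- Team SD 0.1, rater-severity SD 0.3, error SD 0.3, item SD 1.5: 0.01 / (0.01 + 0.09 + 0.09/25) = 0.10. Simulated, the sum-score ICC is 0.09 and the item kappa 0.50.

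The two measures can diverge in either direction.

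**Two recordings.** Take a true ICC of 0.8 and 5 raters. In a one-way model the F ratio is (1 + 4 × 0.8) / (1 − 0.8) = 21 times a central F with 1 and 8 degrees of freedom, whose 2.5% and 97.5% points are 0.00105 and 7.571.

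- Lower: F = 0.022, ICC = (0.022 − 1) / (0.022 + 4) = −0.24.
- Upper: F = 159, ICC = 158 / 163 = 0.97.

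The two-way estimator without rater variance gives, by simulation, about −0.35 to 0.97 (lower limits of −0.34 to −0.36 in separate runs). If half of the non-team variance is between raters, the lower limit is −0.16. With 20 recordings and no rater variance, the range is about 0.63 to 0.89.

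**Recordings needed.** For a 95% confidence interval of total width w, n = 8z²(1 − r)²(1 + (k − 1)r)² / (k(k − 1)w²) + 1. With r = 0.8, w = 0.20 and z = 1.96:

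- k = 3: 1.2293 × 6.76 / 0.24 + 1 = 35.6, so 36.
- k = 5: 1.2293 × 17.64 / 0.80 + 1 = 28.1, so 29.
- k = 10: 1.2293 × 67.24 / 3.60 + 1 = 24.0, so 24.

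**The case against.** Several stronger readings are tempting, and the article does not support them.

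- **A nearly useless tool would be accepted.** The article does not say that significance alone makes the tool acceptable or that the size of kappa will be ignored. What stands is that a significance level is the only criterion named, and it cannot carry that judgement.
- **The score is Likert-based, so kappa is the wrong statistic.** Likert is only an example, and the mention of a checklist and of fulfilled items suggests that some items are yes/no. For those, Fleiss' kappa is suitable. The ordinal weakness applies to an unknown share of the items.
- **Reliability of the total score cannot be estimated.** Two scenarios may mean two case types with several recordings each, and 56 recordings are planned at t0 alone. That reading eases the ICC problem. It also raises N and so lowers the kappa needed for significance: 50 yes/no items on 20 recordings with 5 raters give 1.96 × sqrt(2/20000) = 0.020.
- **Kappa says nothing about the score.** This is too strong, because item agreement is related to the score. It does not establish the score's reliability.
- **Measurement error dilutes the effect.** Random error in an outcome widens the interval of a mean difference and does not shrink the difference. Constant severity differences cancel if the same raters score both time points.

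It is also fair to say that an article can leave detail to a fuller document. The objection here is to the criterion and statistic that the article does name, not to missing detail.

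**Conclusion.** The point holds in this limited form. A test against zero kappa does not demonstrate adequate agreement under any assumed combination: even the most demanding one passes at about 0.25. That conclusion does not depend on the scale of the items or on the meaning of two scenarios. The mismatch between item-level kappa and the analysed total score also stands, although how far they diverge in this tool is unknown. The ordinal weakness is conditional on Likert-type items, and the estimation weakness on two scenarios being two recordings. Every magnitude rests on assumed item numbers, rater numbers, category use and significance level. The expected consequence is mainly lost precision at t0 and t1. Bias would need rater error that differs by time point, and nothing in the article shows that.

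**What to change.** Replace the significance criterion with the size of agreement and its 95% confidence interval:

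- for the total score, a two-way random-effects, absolute-agreement ICC;
- for ordinal items, weighted kappa or an ICC;
- for yes/no items only, Fleiss' kappa.

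State whether two scenarios means two recordings or two case types. Estimate the ICC on a larger subset of the videos already being made at t0 and t1, rated by the experts already planned.

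Set the number of videos from the wanted interval width: about 24 to 36 for a width of 0.20 at an assumed ICC of 0.8, with 10 down to 3 raters. Any minimum limit should be chosen together with that number. For example, requiring a lower limit of 0.6 on 20 videos would, at a true ICC of 0.8, reject the tool in about 27% of cases with 5 raters and 39% with 3 (simulated, one-way interval, no rater variance).

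The cost is rating time. Scenarios last about 10 minutes, so 24 to 36 recordings are about 4 to 6 hours of footage per expert, against about 20 minutes if only two recordings were planned. No new recordings or raters are needed, and the Trials status section says that the tool is still being developed.
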